A few studies have investigated whether coloured lenses reduce hyperexcitability in the visual cortex associated with visual stress and/or migraines using functional neuroimaging and visual evoked potentials [16,18,19]. While some studies support a reduction in the cortical excitability with coloured filters [16] others report conflicting results [19] or only reductions in those with co-existing migraines or headaches [18]. Further work is required to fully understand the aetiology and treatment mechanisms of visual stress and what areas of the visual cortex are specifically hyperexcitable in those with visual stress.

Yet, to date investigations into the efficacy of coloured lenses at ameliorating symptoms of visual stress are scant. Recent systematic reviews conclude that a large-scale double-masked randomised control trial needs to take place to investigate coloured lens efficacy in subjects with visual stress [1,20–22]. Two meta-analyses further highlight the necessity for high quality evidence to strengthen the knowledge base in relation to coloured lens efficacy for those with reading difficulties [23,24]. Furthermore, there is some discrepancy in terms of the clinical versus statistical significance of findings of coloured spectacle lenses efficacy among previous studies. This is demonstrated by the use of percentage reading speed change noted with optimal coloured filter to determine efficacy of coloured lenses, with percentage reading speed change with optimal filters reported as ranging between 0.90% (p = 1.0) [13] and 6.4% (p = 0.03) [12].

Additionally, professional optometric bodies’ management guidance in relation to the practice of colorimetry is guarded, citing a lack of robust evidence to either endorse or reject the practice [25–27]. This protocol will detail the methods employed in a double-masked cross over randomised placebo-controlled trial. This superiority trial aims to test the hypothesis that providing coloured lenses to those with symptoms of visual stress will be effective at improving reading performance and reduce frequency of symptoms experienced whilst reading.

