## Methods and materials

### Study design

This study is designed as a double-masked cross-over randomised placebo-controlled trial of coloured lens efficacy in adults with symptoms of visual stress. The trial design is supported by the Standard Protocol Items: Recommendations for Intervention Trials (SPIRIT) framework (see supporting information S1 File). Participants will be evenly and randomly assigned one of two sets of coloured spectacle lenses for initial spectacle wear for a period of six weeks, followed by wear of an alternate pair of spectacle lenses for a further six weeks. Coloured spectacle lenses will differ in their chromaticity, with the ‘experimental’ coloured lenses, tinted to optimal chromaticity, which are presumed to reduce perceptual distortion symptoms, whilst ‘control’ lenses will comprise a chromaticity similar in perceptual colour appearance to ‘experimental’ lenses, to assist with masking, but differing in chromaticity, such that visual stress symptoms are neither improved nor worsened with use of tint. The ‘Control’ lenses shall therefore act as a placebo. Researchers and participants will both be masked to the spectacle lenses worn. A two week washout between periods of spectacle lens wear will be employed, so that any potential legacy effects of coloured lenses are negated.

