**Fig 1 pone.0309625.g001:**
[figure not shown]
Flowchart of spectacle wear diary questionnaire.

After six weeks of wear, a two week washout period will be initiated. Participants’ spectacles will be collected and stored securely. Washout will ensure potential carryover effects from initial spectacle wear will be eliminated. A two week washout period has been determined appropriate, in line with previous investigations [11,37]. Additionally, research suggests colour memory for a chosen colour is the same after 1-hour as it is after 1-week [58]. An overview of trial visits can be seen in the study flowchart in Fig 2.

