#### Secondary outcome measures: Symptom improvement, reading speed with further reading tests, pattern glare scores and long-term compliance with coloured lenses.

**Reading symptom change:** Prior to commencing wear of coloured lenses, participants will be asked to rate reading symptom frequency on the 6-point Likert scale initially used to recruit participants with symptoms suggestive of visual stress to the trial. After 10 minutes and six weeks of coloured lens wear, participants will be asked to repeat the symptom questionnaire. Additionally, after a two week washout period, participants will be asked to rate reading symptom frequency without the use of coloured lenses.

**Developmental eye movement (DEM) test:** The Developmental Eye Movement Test (DEM) Version 1 (Bernell Ltd, 1987), as summarised by Facchin [62] and Tanke et al. [63], was originally proposed to measure horizontal saccadic function of readers [64] but is now thought to more broadly assess oculomotor function whilst reading [62]. Horizontal and vertical reading speed will be measured. Number of omission, addition, transposition, and substitution errors will be noted and will be used to assist calculating adjusted horizontal and vertical reading speeds A ratio of adjusted horizontal:vertical reading speed will then be determined. The DEM will be completed with and without coloured lenses throughout the trial, owing to the low risk of a learning effect from repeat measures of a test comprising a random series of numbers.

**Test of word reading efficiency (TOWRE):** The Test of Word Reading Efficiency (TOWRE) 1st Edition (Pro-Ed Ltd, Austin TX, 1999) comprises a series of two standardised reading tests which independently assess a participant’s sight-word efficiency and phonemic decoding ability – as discussed further by Torgeson et al. [65]. Reading speed and number of errors made on both subtests will be recorded. A Total Word Efficiency Standard Score will be determined and compared to age-equivalent normative scores and percentiles [65,66]. Reading tests will be completed with and without coloured lenses as detailed in the Schedule of Enrolment.

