### Statistical analyses

The Statistical Package for Social Sciences (Version 29.0; IBM Corporation, USA), software will be used for statistical analysis of reading performance and symptom change with use of ‘experimental’ and ‘control’ precision tints. Kolmogorov-Smirnov tests will be used to assess whether the data follow a normal distribution pattern. Average-measures of Wilkins Rate of Reading Test reading speed performance with the use of ‘experimental’ and ‘control’ lenses will be assessed by repeated measures AVOVA (or the non-parametric equivalent where necessary) testing for both interventions. This will be assessed at three timepoints – baseline measures; initial spectacle collection and after 6-weeks of spectacle wear. Post-hoc analysis using repeated measures ANCOVA testing will be conducted. Covariates in statistical analysis will include: baseline reading speed, the number of errors made in each reading test, number of days spectacle lenses worn, number of hours spectacle lenses worn and number of hours completing concentrated tasks with or without the use of coloured lenses.

Clinically significant improvement noted on the WRRT, will be informed by percentage reading speed improvement with ‘experimental’ lenses, compared to baseline. To date, no validated repeatability values nor defined clinically significant improvement on the test exists in the literature. Therefore, researchers will classify participants’ reading speed improvement by two categories: (i) >5% to 15% improvement; indicating a mild clinical improvement on the WRRT and (ii) >15% improvement; indicating a moderate clinical improvement on the WRRT. These values have been derived from the consensus in the literature, whereby a stricter criterion for reading speed improvement has been applied more recently [3].

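### The primary reading-speed ANOVA runs over three timepoints and names neither an experimental-versus-control contrast nor a period term, and the sample size fits the timepoints rather than the lens comparison

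*Protocol article*

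**What the plan says.** The Study design section sets the comparison: "This study is designed as a double-masked cross-over randomised placebo-controlled trial of coloured lens efficacy in adults with symptoms of visual stress". The Introduction adds that it is a superiority trial, and the control tint is described as the placebo.

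The Statistical analyses section then fixes the primary analysis. Average WRRT speed with the two lenses "will be assessed by repeated measures AVOVA (or the non-parametric equivalent where necessary) testing for both interventions". The levels given are those of time: "This will be assessed at three timepoints – baseline measures; initial spectacle collection and after 6-weeks of spectacle wear". A repeated-measures ANCOVA follows as post-hoc work: "Covariates in statistical analysis will include: baseline reading speed, the number of errors made in each reading test, number of days spectacle lenses worn", then hours worn and hours of concentrated tasks. Neither period nor sequence is listed. Clinical improvement on the WRRT, in categories of over 5% to 15% and over 15%, "will be informed by percentage reading speed improvement with ‘experimental’ lenses, compared to baseline".

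The Sample size calculation section uses a within-factors repeated-measures ANOVA and does not state the number of measurements. The washout is justified by carryover: "Washout will ensure potential carryover effects from initial spectacle wear will be eliminated".

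**The concern.** Superiority over a placebo lens in a crossover is answered by one quantity: the within-participant difference between experimental and control lenses, with the order of wear accounted for. The plan specifies a model, timepoints, covariates and a non-parametric fallback, yet does not say which effect in that model decides the trial. An effect of time over baseline, collection and week 6 is not a comparison with placebo.

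Practice is a plausible rival explanation for a time effect. The WRRT uses 15 recurring words and is read twice per visit at repeated visits. The Outcome measures section alternates the ART-2 passages against learning and argues that the DEM carries a low learning risk. It says nothing equivalent for the primary test. A washout addresses carryover, and does not undo practice.

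At stake is whether a significant primary result could be read as lens efficacy when it is not, and whether the comparison that matters has the stated 90% power.

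**Working it through.** **1. The plan's own sample size.** Inputs from the Sample size calculation section: partial eta squared 0.0355, alpha 0.05, power 0.90, correlation ρ = 0.5, nonsphericity correction 1, N = 59.

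- f = √(0.0355/0.9645) = 0.1919. The printed f of 0.1985 would imply eta squared 0.0379, so the two printed values differ slightly.
- For m levels: λ = N·m·f²/(1−ρ), with m−1 and (N−1)(m−1) degrees of freedom.
- m = 3, f = 0.1919, N = 59: λ = 13.03 on 2 and 116 df, power 90.1%.

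| Levels m | N for 90% (f = 0.1919) | N for 90% (f = 0.1985) |
|---|---|---|
| 2 | 74 | 69 |
| 3 | **59** | 56 |
| 4 | 50 | 47 |
| 5 | 44 | 41 |
| 6 | 39 | 36 |

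Only three levels with eta squared 0.0355 give 59. That matches the three timepoints, not two lenses. Then 59 × 1.10 = 64.9, the stated 65.

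**2. Power for the lens contrast.** The documents give no SD and no expected lens difference, so f is carried over from three levels to two as an assumption. With m = 2 and N = 59, λ = 59 × 2 × 0.0368/0.5 = 8.69 and power is 82.6% (85.1% with f = 0.1985). The equivalent standardised paired difference is 2f = 0.384.

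**3. Practice in a within-lens time test.** Assume an inert lens and a linear gain g (in SD) per visit, so the means are 0, g and 2g. Then λ = N·2g²/(1−ρ), on 2 and 116 df.

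- g = 0.1, ρ = 0.5: λ = 59 × 0.02/0.5 = 2.36, significant in about 25% of trials.
- g = 0.2, ρ = 0.5: λ = 59 × 0.08/0.5 = 9.44, about 78% (a simulation gave 79%).
- At ρ = 0.8 the figures are about 56% and 99%.

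In a separate simulation with practice continuing into period 2, the week-6 experimental-minus-control test stayed at 4.6% to 5.7%.

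**4. Omitting period: precision.** Let π be the period effect in units of the SD of the paired difference. Experimental minus control is shifted by −π in one sequence and +π in the other. With balanced sequences and no period term, the variance becomes 1 + π². For an assumed π = 0.5, the standardised difference falls to 0.384/√1.25 = 0.343, and power at N = 59 falls from 83% to 74%.

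**5. Omitting period: bias.** Given the realised split, bias = π(n₂−n₁)/N, where n₁ is the number starting on the experimental lens. For 35:24 and π = 0.4 it is 0.4 × (−11/59) = −0.075 SD. Averaged over 1:1 randomisation it is zero. The Randomisation and blinding section specifies simple randomisation, which does not force balance. A gap of 11 or more has probability 19% at N = 59 and 21% at N = 65.

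**The case against.** The strongest reply is that testing for both interventions, in a trial called a placebo-controlled superiority crossover, naturally means a lens-by-time layout. Practice then falls on both lenses and largely cancels. In simulation with an inert lens and gains of 0.1 or 0.2 SD per visit, the lens main effect was significant in 5.4% of trials at both sizes, and lens-by-time in 5.9% and 5.0%. This stands. A reader might infer that the trial as written will declare efficacy when the lenses are identical. The documents do not support that: it applies to a time test within one lens and to improvement judged against baseline. What survives is that the deciding effect is not named, and that the sample size points to time.

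Other stronger readings also fail:

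- **That the lens estimate is biased.** Without a period term it is unbiased on average. Bias arises only when sequences are unequal, by chance or through dropout.
- **That the no-lens baseline cell dilutes the lens effect and costs power.** With one shared baseline and an equal effect at both lens visits, estimate and standard error shrink by the same factor. The test equals a paired test on the mean of the two visits.
- **That the fallback is Friedman's test.** That test is named only for pattern glare scores, not for the WRRT.

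The size of any WRRT practice effect is not in the documents. The words are randomly ordered and without context, which may limit it. The practice and period figures are therefore illustrations.

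**Conclusion.** The point holds as a defect of specification in the primary analysis. The protocol fixes an ANOVA over three timepoints without saying that experimental versus control is the test that decides the trial, and without a period term. This is not detail left to an analysis plan, because the article states the model and its timepoints, and the sample size agrees with them.

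The firmest number is that 59 follows from a three-level factor. The 83% power for a two-lens contrast at 59 depends on carrying f over. The 25% and 78% figures depend on assumed practice gains and on a within-lens test. The loss from 83% to 74% depends on an assumed period effect. None of these shows that the trial will reach a false conclusion. They show that the wording permits an analysis that does not answer the superiority question, and that the stated 90% power is not shown for the one that does.

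**What to change.** Before unmasking, amend the Statistical analyses section as follows.

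- Name the within-participant experimental-minus-control WRRT difference, with 95% CI, as the single primary test, at one pre-stated visit such as six weeks.
- Estimate it from a model with lens, period and sequence. Use one value per period. If both visits enter, add a participant-by-period random effect or an unstructured covariance: with a participant effect alone, simulated type I error for the week-6 contrast was 7% to 8% when participant-by-period variance was 0.5 to 2 times the residual.
- Treat no-lens reading speed as a covariate, not as a level of time.
- State that change from baseline within a lens, including the 5% and 15% categories, is not evidence of efficacy over placebo.
- Restate the power for this contrast, with the assumed lens difference, SD and correlation.

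The cost is some extra analysis work, with no new visits or measurements. The stated power is likely to become somewhat less favourable. Recruitment was still open when the article was written (60 enrolled, more screening planned), so the restated power can still inform the target.

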#### Spectacle wear periods and washout.

Participants will wear each intervention for a period of six weeks. Participants will be informed that spectacle wear is voluntary and to wear as much as desired. Participants will be advised to avoid wearing coloured spectacle lenses when driving at night as per manufacturer’s specification [52], to ensure that spectral transmission complies with College of Optometrists’ Guidance for Professional Practice on provision of coloured filters when driving [57]. In the unlikely event of adverse event related to spectacle wear whilst driving, incident(s) will be monitored and reported to the project’s chief investigator [name]. Within the first and final week of spectacle wear, participants will be asked to complete a spectacle wear diary online (Research Electronic Data Capture, version 11.0.3, 2021, or paper copy where necessary) at the end of each day of wear. The diary will record the number of hours the spectacles are worn daily. If the participant indicates that they have not worn the spectacles, they will be asked to provide reasons for this. Participants will also be asked to note the number of hours completing concentrated and/or near-work tasks and if the coloured spectacles have been worn to assist with these tasks. Participants will also be asked to grade how helpful (if at all), the spectacle lenses have been in assisting their reading performance on a six point Likert scale (0 = ‘Not at all helpful’ to 5 = ‘Extremely helpful’). Fig 1 comprises a flowchart of the questions that will be posed to participants in their online spectacle wear diary.

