#### Primary outcome measure: Wilkins rate of reading test reading speed.

The Wilkins Rate of Reading Test (WRRT) is a long established measure of reading speed with and without the use of coloured filters and has been used in previous reading studies [12,28–31]. As discussed in full by Wilkins et al. [59], the test comprises 15-randomly-ordered monosyllabic commonly used English language words that repeat throughout 10-lines of a size 9-point text to form a crowded paragraph. Owing to the random order of words presented devoid of context, the test isolates the visual input of processing words whilst reading, so that neither syntactic nor semantic reading processes are involved [60].

Participants will read the passage of crowded text aloud within 60-seconds, with and without coloured lenses as detailed in Fig 3 – Schedule of Enrolment, throughout the duration of the trial. The number of words-per-minute (wpm) read correctly will be calculated. During each visit an average reading speed from two measures of the WRRT will be calculated. The examiner will note the number of errors made, namely omissions, reversals, additions, substitutions and mispronunciation [59]. In the event of a ceiling effect whereby all 150 words are read correctly in less than 60 seconds, the time taken to complete the test will be noted, and used to calculate equivalent wpm reading speed [59–61]. The number of additional words read correctly and the percentage reading speed change with coloured lenses will be calculated and compared to baseline measures, in order to assess whether a clinically significant improvement in reading speed has occurred. An increase in reading speed of 15% has been deemed clinically significant by the developer of the Wilkins Rate of Reading test [3]. As percentage change is not normalised, effect sizes and confidence intervals will also be calculated from repeated measures.

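### The post-hoc ANCOVA lists covariates that the lenses can change (errors, days and hours worn, task hours), so its adjusted lens contrast need not be the total randomised lens effect

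*Protocol article*

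**What the plan says.** The Statistical analyses section of the protocol article names the main test of Wilkins Rate of Reading Test (WRRT) speed first. Speed with the two lenses "will be assessed by repeated measures AVOVA (or the non-parametric equivalent where necessary) testing for both interventions", at baseline, at spectacle collection and after six weeks of wear. No covariate is named for that test.

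The next sentence adds a second model: "Post-hoc analysis using repeated measures ANCOVA testing will be conducted". The covariate list follows directly: baseline reading speed, then "the number of errors made in each reading test, number of days spectacle lenses worn, number of hours spectacle lenses worn", and last the hours of concentrated tasks, whether or not the lenses were used for them.

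Three other statements show what these covariates are:

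- **Outcome and errors.** The primary outcome section says "The number of words-per-minute (wpm) read correctly will be calculated". The examiner counts errors on the same WRRT readings, which are taken with and without lenses.
- **Wear.** Under Spectacle wear periods and washout: "Participants will be informed that spectacle wear is voluntary and to wear as much as desired".
- **Recording of wear and task time.** Same section: "Within the first and final week of spectacle wear, participants will be asked to complete a spectacle wear diary online". Hours of concentrated or near work come from that diary.

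**The concern.** In a randomised crossover, the contrast between lenses estimates the effect of being given one lens rather than the other. Adjusting for something fixed before the lenses are given leaves that meaning intact. Adjusting for something the lens can alter does not: the model then compares the lenses at equal errors or equal wear, which randomisation did not arrange.

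Here a lens that helps might reduce errors, which raises words read correctly, or might be worn more because it helps. Holding those quantities fixed takes that part of the benefit out of the lens contrast. If something else, such as motivation or a heavy reading period, drives both wear and speed, the adjustment can also create a difference where none exists or enlarge a real one.

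The article gives the ANCOVA no stated purpose, such as mediation or dose-response, and no caution about reading its lens effect. An adjusted lens effect could therefore be reported as efficacy, in a field where the article itself says clinical guidance awaits a large trial.

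**Working it through.** **1. Which stated figure depends on the covariates?** None. The sample size of 59 can be reproduced from the repeated measures ANOVA alone.

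- Inputs (Sample size calculation): partial eta squared 0.0355, correlation 0.5, epsilon 1.0, alpha 0.05, power 0.90. Three measurements (Statistical analyses).
- f² = 0.0355 / (1 − 0.0355) = 0.0368, so f = 0.1919.
- λ = f² × N × m / (1 − ρ) = 0.0368 × 59 × 3 / 0.5 = 13.0, on 2 and 116 degrees of freedom.
- Power is 0.901, and 59 is the smallest N that reaches 0.90. (The printed f of 0.1985 would give 56; that is a separate matter.)

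The stated power therefore belongs to a test without covariates.

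**2. When is each covariate recorded, and can the lens change it?**

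| Covariate | Recorded | Can the lens change it? |
|---|---|---|
| Baseline reading speed | before the lenses | no |
| Errors in each reading test | at every reading, with and without lenses | yes for on-lens readings, which also give the outcome; no for a no-lens baseline count |
| Days worn | diary, first and final week of wear | yes, wear is voluntary |
| Hours worn | same diary | yes |
| Concentrated-task hours | same diary | possibly |

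The diary covers 2 of 6 weeks, so it measures wear over the period only in part. It also starts after the collection visit, so it cannot explain speed measured at that visit.

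**3. What adjustment does to the lens contrast.** For each participant let D be speed with the experimental lens minus speed with the control lens. Let M be the same difference in a covariate, with mean δ. Suppose D = θ + βM + error.

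- Total lens effect: θ + βδ.
- Lens contrast adjusted for M as recorded: θ. The part βδ is lost.
- If s = βδ / (θ + βδ) is the share running through the covariates, the adjusted contrast is total × (1 − s).

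The documents give neither s nor an expected effect in wpm. With a total of 5 wpm as an assumption, and s split equally between errors and wear:

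| Assumed share s | 5 × (1 − s) | Simulated adjusted | Simulated unadjusted |
|---|---|---|---|
| 0% | 5.0 | 4.99 | 5.01 |
| 20% | 4.0 | 3.99 | 4.99 |
| 40% | 3.0 | 3.03 | 5.04 |
| 60% | 2.0 | 2.04 | 5.03 |

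**4. Why the direction is not fixed.** Suppose wear has no effect on speed, but a common cause U moves both: D = τ + γU + error and M = δ + U. Regressing D on M gives slope b, with the sign of γ, and intercept τ − bδ. With no lens effect (τ = 0) the adjusted contrast is −bδ, which is not zero. If U is motivation (γ positive) and the experimental lens is worn more (δ positive), the contrast is pushed down. If U is a spell of worse symptoms that brings more wear and slower reading (γ negative), it is pushed up.

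**5. When the problem does not arise.** If M is centred at its own mean, the intercept is θ + βδ, the full effect. A single centred value per person likewise leaves the within-person contrast largely unchanged. An uncentred per-person value is different again. If D = τ + κ(H − mean H), where H is hours worn, the contrast reported at H = 0 is τ − κ × mean H, the effect at zero hours of wear. The article does not say which form is used.

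**The case against.** The strongest reply is that the primary result is untouched. The main ANOVA names no covariates, and the ANCOVA is introduced after it and called post-hoc. Elsewhere the article uses that term for secondary exploration, namely learning-difficulty profile and chromatic separation between the lenses. Asking whether wear or reading demand relates to response is a reasonable exploratory question. This stands. A reader might infer that the trial's primary efficacy test is biased or loses power, and the text does not support that. The covariate list is introduced in general terms, but it follows the ANCOVA sentence, and the sample size does not rest on it.

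It can also be said that the distortion depends on how the covariates enter, which a condensed article may leave to an analysis plan. This stands too. Attenuation follows for lens-period values entered uncentred, not for every version of the model, so it is wrong to say flatly that the ANCOVA removes part of the effect.

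Two further points are fair. A no-lens baseline error count would be a valid covariate, although a list covering each reading test does not stop there. And the three timepoints are stated for the ANOVA; the article does not say that the ANCOVA keeps baseline as a time level while also adjusting for it.

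What remains is that the choice of covariates was not left to a later document. The article fixes the list and says the analysis will be done, and the post-hoc label alone does not tell a reader that the adjusted lens effect is not the randomised effect.

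**Conclusion.** The point holds within limits. Four of the five listed covariates are, or can be, recorded after the lenses are given and may respond to them. Entered as lens-period values, they make the adjusted lens contrast something other than the total randomised effect. The bias can go either way, and is toward zero if the lens improves accuracy or encourages wear.

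The size cannot be found from the documents. The range of 5.0 to 2.0 wpm rests on an assumed total of 5 wpm, assumed shares of 0% to 60%, and uncentred lens-period covariates. It shows how the mechanism works and is not a forecast.

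Two stronger statements about size may tempt a reader. One is a fall in the trial's power: the trial is not powered on this model, and the adjusted model's power depends on residual variance and collinearity that the documents do not give. The other is that each error avoided would cost exactly one word per minute of measured gain: that needs an error coefficient of exactly −1, whereas the coefficient would be estimated, and additions count as errors without necessarily costing a correct word.

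The primary ANOVA is not shown to be affected.

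**What to change.** Amend the covariate sentence in Statistical analyses as follows:

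- In any model used to estimate the lens effect, restrict covariates to values measured before the lenses are given: no-lens reading speed and, if wanted, the no-lens error count. Include period and sequence.
- Do not use baseline as both a covariate and a time level in the same model.
- Compare errors and wear between the lenses as outcomes in their own right.
- Label any model containing wear, task time or on-lens errors as exploratory and non-randomised, not as an efficacy estimate. State whether its covariates enter per lens period or per person, and whether they are centred.

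The cost is analysis wording only, with no change to data collection or sample size. The change should be made and dated before unmasking.

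### The WRRT clinical-improvement bands are defined for the experimental lenses against baseline only, with no matching control-lens contrast, and the two sections differ on what counts as clinically significant

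*Protocol article*

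**What the plan says.** Three parts of the protocol article bear on this.

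- **Study design.** The control lenses are tinted so as neither to improve nor to worsen symptoms, and they serve as the placebo.
- **Primary outcome measure.** The article says that "the percentage reading speed change with coloured lenses will be calculated and compared to baseline measures", in order to judge whether a clinically significant gain has occurred. It adds: "An increase in reading speed of 15% has been deemed clinically significant by the developer of the Wilkins Rate of Reading test", citing reference 3. Because percentage change is not normalised, effect sizes and confidence intervals from the repeated measures are also promised.
- **Statistical analyses.** WRRT speed with both lenses is compared by repeated measures ANOVA at baseline, spectacle collection and six weeks. The clinical reading is a separate step: "Clinically significant improvement noted on the WRRT, will be informed by percentage reading speed improvement with ‘experimental’ lenses, compared to baseline". The section then says that "no validated repeatability values nor defined clinically significant improvement on the test exists in the literature" and sets two bands: ">5% to 15% improvement; indicating a mild clinical improvement on the WRRT" and ">15% improvement; indicating a moderate clinical improvement on the WRRT". It gives their source as follows: "These values have been derived from the consensus in the literature", with reference 3 cited for the more recent, stricter criterion.

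**The concern.** Randomised lens order balances practice, elapsed time and expectation between the two lenses. It does not balance them between a lens and a baseline reading taken before wear. A participant can cross 5% because the WRRT has become familiar, because any tinted spectacle raises expectation, or because one visit's average happened to be low. The article guards against learning on the ART-2 and argues that the risk is low for the DEM. In the text shown it offers no such argument for the WRRT, which repeats the same 15 words and is read twice at each visit.

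Without the control-lens counterpart, a reader cannot tell how much of a reported share of improved participants is due to the optimal tint. The Introduction itself notes discrepancy between clinical and statistical significance in earlier studies, and the Discussion aims to inform practice. The bands are likely to be read closely for that reason.

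The thresholds add a second difficulty, because the two sections do not agree on what level of gain is clinically meaningful.

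**Working it through.** **1. Plan's own figure.** The article gives no expected proportion of improved participants, no SD or repeatability for WRRT change, and no practice effect. There is nothing to reproduce for this rule. The sample size rests on the ANOVA and does not depend on it.

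**2. Comparator, side by side.**

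| Section | Lens named | Compared with |
|---|---|---|
| Statistical analyses, ANOVA | experimental and control | each other, over three timepoints |
| Statistical analyses, clinical bands | experimental | baseline |
| Primary outcome measure, percentage change | coloured lenses, set not specified | baseline |

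Neither description of percentage change plans an experimental-versus-control comparison of the bands.

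**3. Illustration with an inert lens.**

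Inputs from the article: cuts of 5% and 15%; each visit value is the mean of two reads.

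Assumed inputs, not in the article: single-read within-person coefficient of variation (CV) of 3%, 5% or 8%; mean practice gain of 0%, 3% or 5%; normally distributed percentage change.

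SD of change between two visits, each averaging two reads: sd = CV × √(1/2 + 1/2) = CV.

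Share classed above a cut: P = 1 − Φ((cut − practice) / sd).

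Examples:
- CV 3%, practice 0%, cut 5%: 1 − Φ(5/3) = 1 − Φ(1.67) = 0.048
- CV 5%, practice 3%, cut 5%: 1 − Φ(2/5) = 1 − Φ(0.40) = 0.345
- CV 8%, practice 5%, cut 15%: 1 − Φ(10/8) = 1 − Φ(1.25) = 0.106

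| CV | Practice | Above 5% | Above 15% |
|---|---|---|---|
| 3% | 0% | 5% | <0.1% |
| 3% | 3% | 25% | <0.1% |
| 3% | 5% | 50% | <0.1% |
| 5% | 0% | 16% | 0.1% |
| 5% | 3% | 34% | 0.8% |
| 5% | 5% | 50% | 2.3% |
| 8% | 0% | 27% | 3.0% |
| 8% | 3% | 40% | 6.7% |
| 8% | 5% | 50% | 10.6% |

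The 50% entries follow from setting the practice gain equal to the cut and carry no further information. With no practice gain, noise alone gives 5-27% above the lower cut.

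**4. Sensitivity to the assumptions.** A wider set (combined practice and placebo shift 0-8%, SD of individual change 5-12 percentage points) gives 16-73% above 5%, about 9 to 43 of 59 participants, and 0.1-28% above 15%. The result depends heavily on what is assumed.

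**5. With the control lens classified the same way.** If the lenses do not differ, both have the same expected share above each cut, because lens order is randomised and the reference reading is shared. The expected experimental-minus-control difference is then zero in every scenario above.

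**6. Thresholds, side by side.** A 10% gain falls short of the 15% level cited in the outcome section but is a mild clinical improvement in the analysis section. A gain of exactly 15% meets the cited level in the first and falls in the mild band in the second. One section reports a developer's value from reference 3. The other says no defined value exists, then draws its cuts from a literature consensus and cites the same reference.

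**The case against.** The strongest reply is that the efficacy comparison does not rest on these bands. The ANOVA on the primary outcome uses both lenses, and the sample size is built on it. The article says only that clinical significance is informed by the percentage, and nowhere says that the bands decide efficacy. This stands, and it limits the point to the clinical-significance classification.

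A reader might infer that the rule throws away randomisation and masking. The article does not support that. Participants and researchers stay masked to the lenses, so lens readings that feed the percentages are taken masked. What is missing is a between-lens contrast of the categories.

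The outcome section's reference to coloured lenses may well cover both sets, so control-lens percentages may be calculated, and effect sizes with confidence intervals are promised there. That is fair. The stated contrast is still with baseline, however, and the analysis section names the experimental lenses alone.

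It is tempting to call baseline the least practised reading. The WRRT schedule is in Fig 3, which is not available, so the number of earlier readings, and whether baseline is specific to each period, cannot be checked. A later baseline would reduce practice effects but would not remove placebo response or noise.

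The threshold conflict is partly wording. One developer's view can coexist with the absence of a validated definition, and 15% is a cut in both sections. What remains is the different status given to gains between 5% and 15%. The Introduction's 0.90% to 6.4% range of reported changes is no evidence against the 5% cut: those are study-level results, whereas the cut classifies individuals.

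**Conclusion.** The point holds for the clinical-significance classification only. As written, the rule can label participants clinically improved when the tint is inert, and no placebo counterpart is planned to show it. The primary ANOVA is untouched, and the documents do not support reading this as a flaw in the main efficacy test.

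The size is illustrative. About 5-50% above the lower cut and 0-11% above the upper one rest on an assumed CV of 3-8% and practice gain of 0-5%; other plausible inputs move both ranges considerably. The direction does not depend on those values: any practice gain or placebo response raises the share above a cut, and noise alone puts some participants over it. The threshold wording is a smaller inconsistency that should be settled alongside.

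**What to change.** In Statistical analyses, state that each participant will be classified with the same bands under both the experimental and the control lenses, from the same reference reading. Report the paired experimental-minus-control difference in the proportion above each cut, with a confidence interval. McNemar's test is one suitable choice and is already planned for the symptom scores. The experimental-versus-baseline proportion may be shown descriptively but should not be offered as evidence of efficacy.

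Reconcile the outcome and analysis sections on what counts as clinically significant: whether 15% is the reference level, what status a gain above 5% and up to 15% has, and where exactly 15% falls.

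The cost is a change of wording and one further table. WRRT speed is already planned with both lenses for the ANOVA, so no new measurements or visits are needed.
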